### Outpatient treatment at CREN

All overweight/obese students, Body Mass Index (BMI)-for-age = weight/height in square meters ≥1 Z score, *n* = 138, have been invited to attend outpatient care at CREN with their parents. At the Center, they receive nutritional counseling, clinical care (the frequency is according to the presence/type of comorbidities), and psychological counseling according to the needs identified by the research team and/or family (Fig. 1).

### Description of the outpatient treatment at CREN:

**Nutritional Counseling**
At the first meeting, the dietitian identifies the readiness for change in the patient, according to the methodology of the Transtheoretical Model Test (TTM) for Behavioral Change [20]. After classifying the stage of change, the consultation focus is then nutrition counseling using the strategy of Motivational Interviewing (MI) [11]. MI is a client-centric directive counseling that aims to stimulate behavior change, helping participants to explore and resolve their ambivalence (conflict between two paths to follow, in this case, healthy or unhealthy eating habits) [12]. The dietitian, therefore, does not prescribe eating plans or strategies for calorie control, but focuses on the identification of the state of readiness to change, intervene to reinforce the positive steps taken by the patients and their families, and establish new goals by providing new information on healthy lifestyle. These targets are based on the Guidelines for the Treatment of Childhood Obesity [10, 14, 21] as well as the recommendations of the World Health Organization(WHO) [2] and the Brazilian Food Guide(BFG) [22]. The aims of the strategy are as follows: reducing the consumption of sugary drinks with progressive increase in the intake of drinking water, reducing the consumption of fried and ultra-processed of foods by replacing them with options of raw or minimally processed foods, increasing in the consumption of fruits and vegetables (target of 3 to 5 servings/day), avoiding sedentary lifestyle (decrease screen time to less than 2 h/day), and increasing regular physical activity (60 min goal a day/5 days a week). These targets are reassessed every new visit and redefined or strengthened for the following period.In addition, a 24-h dietary recall is performed during the consultation, as a tool to guide the advice and to setting monthly goals for the patient. The duration of this consultation is 40 min (first visit) and 30 min (return visits).
**Clinical care**
The clinical evaluation is based on the overall assessment of the patient, including physical examination to define the pubertal stage and blood pressure, and evaluation of laboratory parameters. Participants with comorbidities, as for example, diabetes, dyslipidemias, hypertension, insulin resistance, hyperinsulinemia, or hyperglycemia are treated according to the Guidelines of the Brazilian Society of Pediatrics [23]. Participants with orthopedic, dermatological, renal, hepatic, respiratory, or psychological alterations are referred to the appropriate specialists.Patients diagnosed with deficiency/insufficiency of vitamin D (25OHD <20 ng/ml and <30 ng/ml, respectively) are treated with proper supplementation [24]. Participants of the experimental group receive the supplement at school with a dosage of 50,000 IU of cholecalciferol once a week for 6 weeks, receiving gelatinous capsules administered under the supervision of the research team. After the supplementation period (between 30 to 60 days after the end of treatment), serum 25OHD is checked. Participants with serum 25OHD concentrations of ≥30 ng/ml are provided cholecalciferol supplement (D3) of 600 IU/day for maintenance for three consecutive months. Participants who do not achieve recovery of vitamin D deficiency after this period receive further supplementation of 50,000 IU of cholecalciferol, once a week for other 6 weeks, followed by repeat evaluation of D 25OH after this period.
**Psychological Counseling**
Students of the experimental group identified with some significant psychological distress during nutritional or medical appointments and even those actively seeking help are met individually through psychological counseling sessions. In these sessions, the therapist searches jointly with the patients an understanding of their demand and life problem, as well as a possible way to solve it [25].

#### Control group

##### 2.9.1.1.At school

The students in the control group (*n* = 353) participate in weekly meetings with the whole class for the first six months, with the purpose of motivation for adopting a healthy lifestyle (Fig. 1). All students of the 3rd, 4th, and 5th grades participate in these activities. Weekly reflective meetings were conducted by the psychologist, as well as nutrition education workshops led by the two dietitians. In addition, three meetings are held with parents and teachers where the following activities are performed: the importance of having a healthy lifestyle, eating breakfast, and teaching healthy recipes. After this motivation period, all overweight students were referred for outpatient treatment at CREN.

#### Data collection

##### 2.10.1.1.Weight and height

Weight was measured using a digital portable scale (Plenna® brand MEA 07400, São Paulo, Brazil) with a maximum capacity of 200 kg and a precision of 50 g. Participants were weighed using light clothing, without shoes and accessories. Height was measured using a portable stadiometer for field research, with a precision of 1 mm. (Height Exata®, São Paulo, Brazil), with subjects in the vertical position, wearing light clothes, without head garments, undone hairstyle, and head positioned in the Frankfurt plane.

The nutritional status of the students was evaluated by calculating the Z score of the BMI -for-age, using WHO AnthroPlus (version 1.0.4, 2009), at the beginning and at the end of the intervention period (Fig. 1).

##### 2.10.1.2.Mapping of student social network

A map of the social network of the students is being designed according to the methodology described by Sanicola [26], at the beginning and at the end of the intervention period (Fig. 1). This technique used in social sciences allows the mapping of the qualitative (type) and quantitative (number) relationships that make up the relational web of an individual. The map is composed of the primary (friends and family) and secondary (institutions) networks.

People in the primary network groups are united by ties of kinship, neighborhood, and friendship that influence, in some way, the individual’s life condition and choices [27]. It is known that relationships between friends are extremely important for the profile of consumption. The secondary network maps the relationship of the individual to institutions, such as schools, churches, hospitals, among others [26].

The map is developed in the classroom after an extensive explanation and under the supervision of the researcher in charge of the activity. Students are asked to paste on a white sheet colored circles (green = relatives, blue = friends, yellow = neighbors) that represents the number of their relationships. The number of circles and the relationship types are then quantified. The school is considered the secondary network of reference. Students are also asked to write in an ellipse marked in the same white paper the number of colleagues/teachers/employees who they considered friends or with whom they have a personal relationship at the school environment.

### Outcome measures

The nutritional profile of all students will be compared at the beginning and end of the school intervention. The incidence of overweight/obesity will be calculated according to the percentage of participants who were not overweight/obese at the start of the intervention but may be overweight/obese by the end of the intervention period. The prevalence of overweight/obesity will be defined as the number of individuals who remained overweight/obese during the study, and remission will be calculated according to the number of participants who are no longer overweight/obese at the end of the study. In addition, the social network and its evolution over the intervention will be mapped and compared to the nutritional profile.

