**Discussion:**

This study is the first to assess the effectiveness of a multi-component and environmental school-based intervention for the recovery of low-income, overweight/obese children and adolescents. If positive, the results demonstrate the feasibility for the recovery of excess of weight in populations of similar conditions and age.

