### Sample size calculation

A power analysis was conducted based on the changes in standardized BMI. Assuming an alpha error of 0.05, power of 0.80, and mean difference of the delta (post-intervention vs. baseline measurement) of standardized BMI of 0.12 relative to the control group, with a standard error of 0.30, the estimated number of participants need to be studied per group is 98 (total = 196) [16]. The estimated difference of 0.12 in the standardized BMI was based on previous intervention studies in obese children [17].

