### Outcomes

Recovery of BMI (BMI < 1) or a persistent and progressive reduction in BMI throughout the intervention period will be considered as the primary outcome.

Furthermore, the following are the secondary outcomes expected: reduction of waist and neck circumferences, reduction in body fat percentage, reduction in blood pressure, and improvement of the biochemical profile. The following improvements in social variables are also expected: in the proportion of overweight students motivated to maintain healthy eating habits and in achieving the stablished goals, in the proportion of those motivated to maintain physical activity recommendations, on the average quality of life index, in the proportion of students with a positive body image, recovery of the symptoms of food addiction, and the social network communications regarding excess weight.

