### Analysis plan and statistics

The data will be tabulated with double input. Descriptive statistics will be used to correlate all variables, by using mixed analysis models. Adjustments will be made for age, gender, pubertal stages using IBM Statistical Package for Social Sciences (SPSS Statistics Desktop) base 22.0.

Changes in the outcomes will be evaluated using a fixed-effects model, and covariate adjustment will be performed to account for the difference in sizes between both groups. Missing data will be identified in each subgroup. An imputation model based on the Multiple Imputations by Chained Equations (MICE) method will be applied (package MICE 2.25, running on R version 3.3.2) [47]. The imputation model will include all the baseline features in addition to age, gender, and classroom. According to this method, a suitable number of imputation models to account for a 95% CI is 59 (we will assume a worst-case scenario and use the maximum missing proportion). Regarding the number of iterations, as suggested in [48], we will use 5 iterations and the Predictive Mean Matching (PMM) method for every outcome variable. After generating imputed models, they will be pooled according to Rubin’s rule in order to obtain valid statistical inferences [49].

Changes in remission, incidence, and prevalence of obesity in the experimental group and control will be evaluated at the end of the study. Odds ratios adjusted for age, gender, and other baseline measures will also be calculated.

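### The stated primary outcome has no comparator and is not the between-school difference in BMI-Z change on which the sample size rests

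*Protocol article*

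**What the plan says.** Four sections of the protocol article bear on which comparison decides the trial.

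- **Sample size calculation.** The quantity is the mean difference in change from baseline "of standardized BMI of 0.12 relative to the control group", with alpha 0.05, power 0.80 and 98 participants per group. This is a between-school contrast on a continuous measure. The participants are not described further.
- **Outcomes.** Recovery (BMI below 1), or a sustained and continuing fall in BMI, "throughout the intervention period will be considered as the primary outcome". Neither the control school nor the population is named.
- **Outcome measures.** "The nutritional profile of all students will be compared at the beginning and end of the school intervention". Remission is then defined as a number of participants no longer overweight or obese at the end.
- **Analysis plan and statistics.** "Changes in remission, incidence, and prevalence of obesity in the experimental group and control will be evaluated at the end of the study". Adjusted odds ratios are added without saying what they compare. Changes in the outcomes go into a fixed-effects model. None of this is tied to the outcome called primary.

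Both schools identify students with excess weight at BMI-for-age Z ≥ 1, 138 in the experimental school and 125 in the control school. According to the Control group section, the control school receives six months of class sessions, after which its overweight students are referred for outpatient care.

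**The concern.** The sample size rests on one quantity and the outcome text describes another. A reader who takes the Outcomes section at its word would look for students who recovered, or whose BMI fell, and could find them in the experimental school whatever happened in the control school.

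Two features make that reading unsafe here. First, recovery is judged against the same cut-off that selects the students, so some who were just above 1 at baseline will be below 1 at the end through ordinary within-child variation. Second, the control school also receives active components, so improvement in both schools is plausible and says nothing about the added school programme.

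Even if everything is compared between schools, the primary outcome can be met by recovery or by a fall in BMI. If either result may be called positive at 0.05, the error rate assumed in the sample size is not kept.

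**Working it through.** **1. Which contrast does the sample size fix?** Inputs from Sample size calculation: difference 0.12, spread 0.30, alpha 0.05, power 0.80. The text gives the spread "with a standard error of 0.30", but the figure of 98 follows only if 0.30 is the standard deviation of the change.

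- Two-sided, between groups: n per group = 2 × (1.960 + 0.842)² × 0.30² / 0.12² = 98.1. This reproduces the stated 98.
- One-sided, between groups: 2 × (1.645 + 0.842)² × 0.30² / 0.12² = 77.3.
- Two-sided, within one group: (1.960 + 0.842)² × 0.30² / 0.12² = 49.1 (about 51 with a t correction).

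Of these, only the two-sided between-school difference in change gives 98.

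**2. How much recovery appears with no effect?** From the document: 263 of 791 students (33.2%) at Z ≥ 1, and change SD 0.30. Assumptions not in the document: no effect, no drift, BMI-Z normal with equal SD s at both times, s from 1.0 to 1.4, and the recovery criterion read as Z below 1.

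- The baseline-to-end correlation r follows from 0.30² = 2s²(1 − r), so r = 1 − 0.09/(2s²). This gives 0.955, 0.969 and 0.977 for s = 1.0, 1.2 and 1.4.
- The cut-off lies 0.433 SD above the mean, so the selected students average 0.363/0.3325 = 1.092 SD above the mean.
- Expected mean change in the selected students is −(1 − r) × s × 1.092.
- The share falling below 1 comes from simulating the bivariate normal distribution.

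| BMI-Z SD | r | Mean change, Z ≥ 1 | Apparent recovery | Of 138 |
|---|---|---|---|---|
| 1.0 | 0.955 | −0.049 | 13.1% | 18 |
| 1.2 | 0.969 | −0.041 | 10.9% | 15 |
| 1.4 | 0.977 | −0.035 | 9.3% | 13 |

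The change SD of 0.30 implies a high correlation. If the correlation were 0.80 to 0.95 instead, apparent recovery would be about 14% to 28%, so the size depends on this input.

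**3. What do two interchangeable between-school primaries cost?** Take BMI-Z change and recovery, each tested two-sided at 0.05, with either one sufficient. If independent, the family-wise error is 1 − 0.95² = 0.0975. From the bivariate normal it is 0.091 at correlation 0.5 and 0.078 at correlation 0.8.

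**4. Is the contrast that was sized feasible with the students enrolled?** With 138 and 125 students, the standard error is 0.30 × √(1/138 + 1/125) = 0.0370 and 0.12/0.0370 = 3.24. Nominal power is Φ(3.24 − 1.96) = 0.90, ignoring clustering within the two schools.

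**The case against.** The best reply is that the comparator is evident from the design. Study design calls the trial controlled, the sample size is stated relative to the control group, and the analysis section names both groups. On this view Outcome measures only says when the profile is taken and how incidence, prevalence and remission are counted, and Outcomes defines a variable and not a test. The population is also largely implied: the aim is recovery of overweight or obese students, and only a student at or above 1 can recover to below 1. The article is condensed, and a full analysis plan may name the model term and rank the secondary comparisons.

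Much of this stands. A reader might infer that the trial will be decided by a before-after test in the experimental school, or that a positive result will be declared on any of many comparisons. The documents do not support either inference. No section plans a within-school significance test, the closing sentence of the abstract is not a decision rule, and incidence and the all-student comparison are not part of the outcome called primary.

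What does not fall away is the mismatch in the article's own text. It states a primary outcome, and that outcome is not the quantity it sized. An unseen analysis plan may add detail, but it does not make these two statements agree.

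**Conclusion.** The point holds as a mismatch between the stated primary outcome and the powered contrast. It does not show that an invalid test is planned. The sample size arithmetic is sound for a two-sided between-school difference in change, once 0.30 is read as a standard deviation. The primary outcome as worded has two routes and no comparator or population.

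Under the assumptions given, about 9% to 13% of students with Z ≥ 1 would appear to recover and the mean change would be about −0.035 to −0.049 Z with no effect at all. A recovery rate in one school is therefore not evidence of effectiveness. If both routes are tested between schools and either suffices, the family-wise error is about 0.08 to 0.10. The recovery and mean-change figures rest on assumed normality, an assumed BMI-Z SD and the document's change SD; the error-rate range rests on an assumed correlation between the two tests of 0 to 0.8.

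**What to change.** - **Outcomes and Analysis plan and statistics:** name a single primary contrast, the experimental-minus-control difference in change in BMI-for-age Z from baseline to 16 months among students with Z ≥ 1 at baseline (138 and 125), two-sided at 0.05. This matches the measure and comparator in the sample size section. The population has to be stated, because that section does not name one.
- **Same sections:** keep between-school recovery or remission as the key supportive outcome. Label incidence, prevalence and the all-student comparison as supportive too.
- **Outcome measures:** call beginning-versus-end comparisons within a school descriptive.

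The change is to wording and needs no new data or larger sample. Its cost is real, though: recovery moves from primary to supportive, and improvement within one school can no longer support a claim of effectiveness. A between-school contrast removes regression to the mean and shared change only as far as they are alike in both schools. It does not remove confounding from having one non-randomised school per arm.

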#### Data collection of students with excess of weight (*n* = 263)

Data collection of students with excess of weight (overweight/obese) from experimental and control groups occurred at the beginning of the study and will be repeated 16 months after the initiation of intervention. Figure 1 contains the information that is being collected. Additionally, Table 2 describes the methods used to evaluate biochemical parameters.

**Table 2 Tab2:** Biochemical evaluation

Test	Technique/Machine/Manufacturer	Measures
Complete BloodCount	CITOQUÍMICO/ISOVOLUMÉTRICO/	Variável de acordo com cada componente do exame
Glutamicoxalacetic transaminase(SGO-T)	CINÉTICO–IFCC/AU5800BeckmanCoulter /	U/L
Glutamic-pyruvictransaminase(SGP-T)	CINÉTICO–IFCCWAU5800/BeckmanCoulter	U/L
Gamma-Glutamyltransferase(GGT)	CINÉTICO–SZASZ/AU5800/BeckmanCoulter	U/L
Total cholesterolandfractions	COLORIMETRICO-PEROXIDASE /AU5800/BeckmanCoulter	mg/dl
HDL	COLORIMETRICO–ENZIMÁTICA/AU5800/BeckmanCoulter	mg/dl
VLDL	EQUAÇÃO DE FRIEDWALD/AU5800/ Beckman Coulter	mg/dl
LDL	EQUAÇÃO DE FRIEDWALDAU5800/Beckman Coulter	mg/dl
Calcium	COLORIMETRICO/AU5800/BeckmanCoulter	mg/dl
Phosphor	COLORIMETRICO/AU5800/BeckmanCoulter	mg/dl
Alkalinephosphatase	AMP IFCC/AU5800/Beckman Coulter	U/L
Fastingblood glucose	COLORIMETRICO ENZIMÁTICO/AU5800	mg/dl
PTH	QUIMIOLUMINESCÊNCIA/Architect/Abbott	pg/ml
Insulin	QUIMIOLUMINESCÊNCIA/Architect/Abbott	U/L
Uric acid	ENZIMATICO–URICASE/AU5800/BeckmanCoulter	mg/dl
Creatinine	COLORIMETRICO–JAFFE/AU5800/Beckman Coulter	mg/dl
Albuminuria (isolated sample)	IMUNOTURBIDIMETRIA/AU5800/BeckmanCoulter	mg/g/creatinina na urina
Vitamin D3–25 hidroxicholecalciferol	QUIMIOLUMINESCÊNCIA/Architect/Abbott	ng/ml

### Circumferences and body composition

Measurements of the circumference of the neck, waist, hip, and calf are performed using an inelastic fiberglass band (Sanny®, American Medical do Brasil Ltda) with accuracy of 1 mm. The circumference of the neck is measured below the laryngeal prominence, perpendicular to the largest axis of the neck. The waist circumference is measured by the diameter at the midpoint between the last costal border and the iliac crest [28]. To evaluate abdominal fat, values above the 80th percentile (P80) will be considered as accumulation of abdominal fat (Taylor et al. 2000). Hip circumference is measured at the level of maximal extension of the gluteus [29]. All circumference measurements are repeated twice and registered immediately after reading the measurements. Tricipital, subscapular, and calf skinfolds are measured using a skinfold caliper (Sanny®, American Medical do Brasil Ltda) with 0.5 mm accuracy according to Lohman recommendations [30]. Both triceps and subscapular skinfolds are measured with the students standing erect and the arms naturally hanging. All skinfolds are measured on the right side, in triplicate.

The percentage of body fat (% GC) will be estimated from the sum of triceps, subscapular, tricipital, and calf skinfolds, using the predictive equations proposed by Slaughter et al. 1988, and Hoffman et al. 2012 for Brazilian students [31, 32]; and through Bioelectrical impedance (Biodynamic Body Composition Analyzer, model 310, version 8.01- Biodynamics Corporation, Seattle, USA). This evaluation is performed with the student lying for five to 10 min in the supine position on an insulated mat of electric conductors, without carrying any metallic object, with the legs apart, hands open, according to the methodology described by Lukaski et al. [33]. Students and their caregivers receive prior guidance for proper preparation in the hours prior to the test, i.e., avoiding consumption of alcohol and caffeine (coffee, tea, chocolate) 24 h before the test, not engaging in intense physical activity, avoiding any heavy meal 4 h before the test, and urinating about 30 min before the test.

### Blood pressure

Blood pressure is measured using an oscillometric device (OMROM-HEM-Healtcare 7113® Intellisense –OMRON, DALIAN CO, LTD-CHINA). The measurement is done on the right arm, supported at the level of the heart. Three measurements are taken with a 2-min interval between them, with the student previously relaxed sitting with his back on the chair and feet resting on the floor in an isolated room. Blood pressure will be classified according to the mean of the measurements; analyzed in percentiles, according to age, gender and height; and compared to the values published in the National High Blood Pressure Education Program, 2004 [34].

